### Data collection and management

Two trained research assistants blinded to the treatment groups allocation will record the baseline characteristics of all participants, and the results of the facial expression muscle thickness ratio of affected/healthy side tested by B-ultrasonography at the baseline (week 0) and follow-up 1 (week 10). They will also evaluate and record the HB Grade and Lip mobility score at weeks 0, 4, 8, 10 and 12. Safety assessment and adverse events will be recorded every week starting from week 1 to week 12. Data from this trial will be collected in the CRF. Authorized researchers will record changes in the CRF and provide the date, reason, and signature. Two independent researchers blinded to the group will input the CRF data into an Excel spreadsheet, then cross-check the data.

Hardcopy data will be stored in a secure locker, and electronic data will be encrypted and stored in a specified computer. Only the principal investigator will have access to all documents, protect the electronic documents using a password, and create backups for all documents. The First Affiliated Hospital of Zhejiang Chinese Medical University will be responsible for data storage and management.

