### Outcome measures

#### Primary outcome measure

As the primary outcome measure, B-mode ultrasonography will be used to measure facial expression muscle thickness ratio of affected/healthy side.

The operator will use the muscle thickness of both sides of frontal muscle and depressor anguli oris muscle to calculate the affected/healthy side ratio.
Four test points will be on both sides of the frontal muscle and depressor anguli oris muscle (Fig. 5).Detailed procedure: The examination will be performed in a quiet room with low light and at constant room temperature. Participants will lay still for 5 minutes before test. During measurements, participants will lay on the examination bed on their back, keeping their mouths closed and relaxed without making any other expression. An experienced B-mode ultrasonographer will take all measurements.Equipment: GE Logiq9 real-time ultrasonic diagnostic instrument will be used to obtain the measurements. M12L will be used as the probe at a frequency of 5~14MHz and a main frequency of 10MHz.Timepoint of the test: Two measurements will be taken: pre-treatment and at follow-up 1 (week 10).

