#### Secondary outcome measures

House-Brackmann Grade, the severity of facial paralysis will be assessed using the HB Grade at weeks 0, 4, 8, 10, and 12. Grade I (normal function) to VI (total paralysis) will be evaluated based on the facial function at rest and with effort.Lip mobility score. Lip mobility will be assessed using the lip-length index (LL-index) and snout index (S-index) at weeks 0, 4, 8, 10 and 12. The LL-index will be calculated by determining the percentage change in lip length between grinning and resting. The S-index will be calculated by determining the percentage change in lip length between puckering and resting. Lip length will be measured by determining the inter-commissural length.

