## Discussion

Acupuncture is widely used to treat PFP after the acute stage in China [27–29]. It is commonly used to treat FEMA after PFP. However, many patients find it difficult to adhere to it since it requires about three treatments per week. TEA is a new type of acupuncture with a low treatment frequency (once a week). The suture threads, such as polyglycolic acid which has good biodegradability and biocompatibility [30], are widely used in TEA in China. The TEA-embedded thread can increase the tensile strength and stimulate myoblast formation in connective tissues [21, 31], which is considered to be the basis for the clinical application of this treatment.

Herein, STEA is used to determine the effect of specific intervention factors. STEA will be applied to minimize the needle insertion effect since the penetration of traditional acupuncture can be used to treat muscular atrophy. Participants, assessors, and statisticians will be blinded to the groups to minimize comparison bias.

B-ultrasonography is widely used to measure muscle or other soft tissues and disease diagnosis [32]. It is a sensitive detection method for facial muscle thickness and safe, non-invasive, simple to operate, and cost-effective [33–35]. Studies have shown that normal humans have no significant differences in bilateral expression muscle thickness [36, 37]. Therefore, the thickness of healthy facial expression muscles can be used to detect the atrophic facial expression muscle side. Herein, the test was performed at weeks 0 and 10. The final test will be set at two weeks after treatment because improvements of the muscle structure and strength need a long time for recovery.

Moreover, facial expression muscle function recovery is essential for the evaluation of FEMA treatment using TEA. The physical functions will be assessed via H-B Grade and lip mobility score as the secondary outcome measures.

However, this study has some limitations since it is not designed for a stratified study. There are differences in FEMA recovery after PFP with different disease courses. Stratified observation can screen out the best efficacy group with certain disease courses, giving accurate guidance of TEA timing for clinical treatment of FEMA after PFP.

In summary, this study will evaluate the efficacy and safety of TEA for FEMA after PFP. These findings will enhance understanding of TEA as a therapeutic option for FEMA patients after PFP.

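### The two assistants who rate H-B Grade and lip mobility also record the ultrasound ratio, so the week-12 ratings, and possibly those at week 10, may be made with knowledge of the primary result

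*Protocol article*

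**What the plan says.** Three sections of the protocol article bear on this.

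- **Data collection and management** gives two tasks to one pair of people. "Two trained research assistants blinded to the treatment groups allocation will record the baseline characteristics of all participants", and in the same sentence they are also to record "the results of the facial expression muscle thickness ratio of affected/healthy side tested by B-ultrasonography", at week 0 and week 10. The next sentence adds the functional outcomes: "They will also evaluate and record the HB Grade and Lip mobility score at weeks 0, 4, 8, 10 and 12".
- **Primary outcome measure** has someone else do the scanning: "An experienced B-mode ultrasonographer will take all measurements". The scans are before treatment and at week 10.
- **Secondary outcome measures** describes the two functional outcomes. H-B Grades I to VI "will be evaluated based on the facial function at rest and with effort", which makes the grade an observer's judgement. The lip-length and snout indices are percentage changes in a measured distance between the mouth corners.

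The Blinding section keeps allocation with the clinical research coordinator. It also forbids data managers, statisticians, therapists and interviewers to pass allocations or other important information to one another.

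**The concern.** Blinding a rater to treatment arm protects against expectations about the arm. It does not protect against expectations that come from another outcome of the same patient. An assistant who has entered a favourable thickness ratio may, without knowing the arm, lean towards a better facial grade.

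If the ratio differs between arms, for whatever reason, that leaning is spread unequally over the arms, and part of the ratio difference reappears as a difference in function. Within patients it would also strengthen the apparent link between muscle thickness and function. At stake is how far the late functional results can be read at face value beside the ultrasound result.

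**Working it through.** The point itself rests on no stated figure, so the check sets the passages side by side.

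**Step 1: do the same people hold both tasks?** Yes. The subject of the sentence on functional rating refers back to the two assistants who record the ratio. The overlap is stated, not inferred from silence.

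**Step 2: does any safeguard mask them to the ratio?** None in the article.
- Their blinding is to allocation.
- The rule in the Blinding section restricts communication between different roles. It cannot separate two tasks held by the same role.
- The ultrasonographer takes the measurements, but recording the ratio is given to the assistants.

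**Step 3: what could the rater know at each visit?**

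| Week | Ratio recorded at this visit | Function rated | Ratio the rater could know |
|---|---|---|---|
| 0 | Baseline | Yes | Baseline only; randomisation comes after the baseline evaluation |
| 4 and 8 | None | Yes | Baseline only |
| 10 | Follow-up | Yes | Follow-up value, if the scan comes before the rating; the order is not stated |
| 12 | None | Yes | Follow-up value, already recorded by the pair; how they divide patients is not stated |

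The ratings at weeks 0, 4 and 8 cannot be influenced by a week-10 result. The exposure is likely at week 12 and possible at week 10.

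**Step 4: how would knowledge of the ratio become a difference between arms?** Write the rating as true function plus λ times the known ratio, where λ is the pull that the known ratio exerts on the rater. Then:

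arm difference in rating = true arm difference in function + λ × arm difference in ratio.

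The second term is zero if the rater is masked to the ratio (λ = 0) or if the arms do not differ on the ratio. Otherwise it is not zero, even with perfect blinding to arm.

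**Step 5: can the second term be sized?** No. The article gives nothing from which λ could be taken. The Sample size section gives a mean difference of 21.54 and a standard deviation of 23.30, but does not say which outcome they describe, so they cannot be assumed to be the expected difference in the thickness ratio.

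**Step 6: are both functional outcomes equally exposed?** No. H-B Grade is a judgement and λ could be appreciable. The lip indices come from a measured length and leave less room for expectation.

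**The case against.** The strongest case on the other side has four parts.

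- **A condensed article leaves the order of tasks and the CRF layout to the full protocol.** This stands for the order at the week-10 visit, whose absence is not an error. It does not remove the point, because the article itself gives both tasks to the same pair.
- **The raters do not know the arm.** True, and this is not an unblinding fault. Bias between arms can arise only through an arm difference in the ratio. The limit is real, but a trial designed to detect such a difference has to plan for it.
- **Exposure is not established.** A reader might infer that the ratings at weeks 10 and 12 are definitely made with the primary result in hand. The article does not support this. The week-10 order is not given (the schedule figure is not shown), and it is not said that the assistant who enters a patient's ratio also rates that patient.
- **The article never claims that function independently confirms the ultrasound finding.** Also true. The Discussion calls recovery of function essential for evaluating the treatment, but then says only: "The physical functions will be assessed via H-B Grade and lip mobility score as the secondary outcome measures". A reader might infer a promise of independent confirmation; the text makes none.

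A reader might also suspect that these assistants learn of adverse events that hint at the arm, such as local nodules. The article says that adverse events are recorded weekly but does not say by whom, so that inference is not supported.

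**Conclusion.** The point holds in a limited form. One pair of assistants records the primary result and rates the functional outcomes, and the article states no masking of the raters to that result. The week-12 ratings may be influenced by it, and so may the week-10 ratings if the scan is done first. The main exposure is H-B Grade; the lip indices are less exposed.

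The conclusion assumes that recording the ratio means seeing it, and that at least some patients are rated by an assistant who has seen their week-10 value. Both are natural readings of the text, but neither is certain. No size can be put on the bias: any inflated false-positive rate would rest on an assumed λ and on an assumed arm difference in the ratio. The primary outcome is not affected. This is a cheap improvement to the protection of secondary outcomes, not a fault that undermines the trial.

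**What to change.** In Data collection and management, make two changes.

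1. The ultrasonographer named under Primary outcome measure enters the thickness values on a separate CRF page. The two assistants do not see that page until the patient's week-12 functional ratings are signed.
2. At week 10, H-B Grade and lip mobility are completed and signed before the scan.

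The cost is one separate CRF page and a fixed order of tasks at the week-10 visit, with no added staff, visits or patients. Trial status reports ten patients under treatment and recruitment running to March 2022, so a change made at that stage would cover most of the planned 56. For patients already rated under the existing arrangement, the trial report should say that the raters were not masked to the ratio.

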### Data processing and statistical analysis

Following the intention-to-treat principle, data processing and analysis will be performed at the Clinical Evaluation and Analysis Centre of The First Affiliated Hospital of Zhejiang Chinese Medical University. These analyses will be performed on the base of a full analysis set (FAS) and a per-protocol set (PPS). All efficacy analyses will be performed using a FAS, which will consist of all patients who passes the randomized stage and who receives at least one intervention. Last observation carried forward (LOCF) analysis will be used for missing data imputation. The PPS will be considered as a supportive analysis. The results of FAS and PPS analyses will be compared to ensure that the results are consistent. A generalized linear mixed-effect model will be used for sensitivity analysis via the PPS. A subgroup analysis will be conducted following the Kellgren–Lawrence grade.

Quantitative results will be described by the mean, standard deviation, median (quartile 3–1, Q3–Q1), minimum, and maximum, while qualitative results will be expressed as total number and percentages. Grade results with rank meaning will be described via both quantitative and qualitative methods.

The chi-square test will be used to compare the primary outcomes between the two groups. The Wilcoxon rank-sum test will be used to compare ranked data and the independent samples t-test for secondary outcome measures to analyze continuous variables. The incidence of adverse events will be determined and compared between the two groups for safety outcomes. A p-value of <0.05 will be considered statistically significant. SPSS Statistics V.22.0 will be used for all analyses. An interim analysis will be conducted when 50% of the randomized patients completed the primary outcome measurement.

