### Dropout criteria

Poor compliance to the treatment (cannot finish 8-week treatment for personal reasons).Patients experiencing severe adverse events, complications, or special physiological changes.Voluntary dropout.

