### Sample size

The sample size was based on previous similar studies [26], and advice from an expert group. The formula below was used to determine the sample size in each group (28 participants) (alpha (significance level), power (1-beta), dropout rate, and group sample ratio were 0.05, 0.90, 10%, and 1:1, respectively). σ indicates standard deviation (23.30) and d represents the mean difference between the two groups (21.54):
$$ \mathrm{n}=2{\sigma}^2{\left({\mathrm{Z}}_{\alpha /2}+{\mathrm{Z}}_{\beta}\right)}^2/{\mathrm{d}}^2 $$

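### With the primary outcome measured only at weeks 0 and 10, LOCF sets every missing change to zero, and the stated checks do not isolate the effect

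*Protocol article*

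**What the plan says.** All points are in the Protocol article.

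- **Measurement times.** Primary outcome measure: "Two measurements will be taken: pre-treatment and at follow-up 1 (week 10"). Data collection and management agrees: the ratio is "tested by B-ultrasonography at the baseline (week 0) and follow-up 1 (week 10").
- **Analysis set.** Data processing and statistical analysis: "All efficacy analyses will be performed using a FAS, which will consist of all patients who passes the randomized stage and who receives at least" a single treatment. Patients who leave early are therefore in the main analysis.
- **Missing data.** Same section: "Last observation carried forward (LOCF) analysis will be used for missing data imputation". No outcome is exempted.
- **Checks.** Same section: "A generalized linear mixed-effect model will be used for sensitivity analysis via the PPS", and "The results of FAS and PPS analyses will be compared to ensure that the results are consistent".
- **Dropout.** Dropout criteria include "Poor compliance to the treatment (cannot finish 8-week treatment for personal reasons"), severe adverse events and voluntary withdrawal. The Sample size section allows for 10% dropout.
- **Expected course.** Concurrent treatment gives both arms acupuncture twice a week and describes it as effective for the sequelae of facial paralysis.

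**The concern.** Carrying the last observation forward presupposes a post-baseline observation to carry. The thickness ratio has only one, and it is the one that is missing. For this outcome the rule becomes baseline carried forward: the patient is analysed as if a change of exactly zero had been observed, however much of the eight-week course was completed. For H-B grade and the lip indices, measured at weeks 0, 4, 8, 10 and 12, it remains ordinary LOCF.

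A zero change fits poorly with the article's own expectation that the background acupuncture helps in both arms. The imputed zeros pull each arm's mean towards no change, in proportion to that arm's dropout and its true gain. If either differs between arms, the treatment difference is biased.

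The planned checks would not show this. The per-protocol set (PPS), on its usual meaning, leaves out most of the patients whose values were imputed, so a mixed model fitted there says little about the imputation. Comparing FAS with PPS results changes the population and the missing-data handling together, so neither agreement nor disagreement can be attributed to LOCF.

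**Working it through.** **Inputs.** From Sample size: SD 23.30, difference 21.54, and "alpha (significance level), power (1-beta), dropout rate, and group sample ratio were 0.05, 0.90, 10%, and 1:1, respectively". Assumed, because the article does not give them: the mean change in each arm, any dropout rates other than 10%, and that the SD and difference are on the scale of the change in thickness ratio.

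**Reproducing the plan's figure.** n = 2 × 23.30² × (1.960 + 1.282)² / 21.54² = 24.6, rounded up to 25 per group. 25 / 0.9 = 27.8, rounded up to 28. This matches the stated 28 per group. At 10% dropout, 0.10 × 28 = 2.8, so about 3 patients per arm would be imputed.

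**Bias formula.** Let pT and pC be the proportions without a week-10 scan on TEA and sham, and muT and muC the true mean changes. If dropouts would have changed like completers, the expected estimate under baseline carried forward is

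(1 − pT) × muT − (1 − pC) × muC,

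and the bias is pC × muC − pT × muT. It favours TEA only if pC × muC exceeds pT × muT.

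**With a true difference of 21.54** (assumed muC = 5, muT = 26.54):

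| Dropout TEA / sham | Expected estimate | Bias |
|---|---|---|
| 10% / 10% (planned) | 0.90 × 26.54 − 0.90 × 5 = 19.39 | −2.15 |
| 20% / 5% (hypothetical) | 0.80 × 26.54 − 0.95 × 5 = 16.48 | −5.06 |
| 5% / 20% (hypothetical) | 0.95 × 26.54 − 0.80 × 5 = 21.21 | −0.33 |

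Power was simulated with 28 per arm, 40,000 trials per scenario and a two-sided t-test on change at 0.05.

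- 28 complete patients per arm: about 0.925.
- 10% / 10% with baseline carried forward: about 0.88. A complete-case test at the same dropout has about 0.895, so the imputation rule itself costs about 1.5 percentage points.
- 20% / 5%: about 0.75.
- For an assumed sham gain of 0, 10 or 20, power at 10% / 10% is 0.89, 0.87 or 0.83.

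**With no true difference.**

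- Both arms gain 15, dropout 5% TEA / 20% sham: 0.20 × 15 − 0.05 × 15 = +2.25 points in favour of TEA, with type I error of about 6.5–7%. Reversing the dropout reverses the sign.
- Same dropout, both arms gain 0, 10 or 20: spurious difference 0, 1.5 or 3.0, and type I error 5.0%, 5.9% or 7.9%.
- Both arms gain 15 with equal 10% dropout: no bias, and type I error stays at about 5%.

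**The case against.** The strongest reply is that little is lost at the dropout the trial plans for. With 10% in each arm the bias is towards the null, about three patients per arm are affected, and the power cost against complete cases is about 1.5 points. Quoting the fall from 0.925 would overstate it, since most of that loss comes from having missing data at all. This stands, and it limits the severity.

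A reader might infer that TEA is favoured whenever sham loses more patients. The formula does not support that. With gains of 26.54 and 5, even 5% versus 20% dropout leaves the estimate at 21.2, below 21.54; sham dropout would have to exceed TEA dropout by a factor of 26.54 / 5 = 5.3.

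A reader might also infer that strongly unequal dropout is expected. Nothing in the article says so: the arms share points, schedule and needle insertion and differ only in the thread, participants are blindfolded, and acupuncture is given to both partly to support adherence. The 20% and 5% figures are illustrations only.

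It may be said that the FAS versus PPS comparison already sets imputed results against completers. It gives some information, but cannot separate imputation from selection. The article does not define the PPS, so the statement that it omits most imputed patients rests on usual practice.

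Finally, moving the mixed model to the FAS would not by itself cure the problem. With one post-baseline ratio per patient, someone who misses week 10 contributes only a baseline value, and the model comes close to a complete-case analysis.

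**Conclusion.** The point holds, as a should-fix. For the primary outcome the stated rule is baseline carried forward, and it biases the estimate whenever pC × muC differs from pT × muT. At the planned balanced dropout the effect is moderate and conservative: 21.54 becomes about 19.4. With unequal dropout it can go in either direction and can produce a small spurious effect, which the stated checks would not isolate.

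The sizes assume that dropouts would have changed like completers, that the SD and difference in Sample size are on the ratio scale, and that the analysis is a t-test on change. The article names a chi-square test for the primary outcome, which is a separate matter. The description of LOCF as baseline carried forward depends on none of these; it follows from the two measurement times. Nor is this detail left to an unseen analysis plan, since the article itself fixes both LOCF and the per-protocol model.

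**What to change.** In Data processing and statistical analysis, for the primary outcome:

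1. Replace LOCF with an FAS analysis under missing at random, by multiple imputation of the week-10 ratio. Impute from treatment arm, baseline ratio, and whatever H-B grades and lip indices were collected. For patients who leave during treatment these will mainly be the week 4 and week 8 values.
2. Keep baseline carried forward as a named sensitivity analysis.
3. Run a missing-data sensitivity analysis on the FAS, for example a delta or tipping-point analysis that lets the imputed changes differ by arm. The PPS analyses can stay as supportive, but should not be the only check.

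The cost is revised analysis wording and slightly more programming. The predictors are already scheduled and the sample size of 28 per group does not change. With about three patients imputed per arm, the expected gain is protection against undetected bias rather than a large gain in precision. The article reports recruitment still in progress, so the change can be made before unblinding.

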### Study subjects

#### Participants and setting

Patients with FEMA after PFP will be recruited. This study will be conducted in the First Affiliated Hospital of Zhejiang Chinese Medical University.

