#### Inclusion criteria

Patients will be eligible for the study if they:
Male or female patients aged 18–65 years.Patients diagnosed with peripheral facial paralysis ≥3 months before screening.Patients with H-B Grade ≥III.Patients with atrophic facial expression muscles as revealed by B-mode ultrasonography. The muscle thickness of the affected side/healthy side ≤ 90%.

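### The only stated subgroup analysis is by Kellgren–Lawrence grade, which nothing in the visible protocol collects or uses, so it cannot be run as written

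*Protocol article*

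**What the plan says.** In the protocol article, the section Data processing and statistical analysis states: "A subgroup analysis will be conducted following the Kellgren–Lawrence grade". No other subgroup analysis is stated, and no categories or test are attached to this one.

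Other sections show what the trial studies and records:

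- Participants and setting: "Patients with FEMA after PFP will be recruited".
- Inclusion criteria: "Patients with H-B Grade ≥III", together with a facial paralysis diagnosis at least three months before screening.
- Primary outcome measure: "B-mode ultrasonography will be used to measure facial expression muscle thickness ratio of affected/healthy side". This is the only imaging described.
- Secondary outcome measures: "the severity of facial paralysis will be assessed using the HB Grade at weeks 0, 4, 8, 10, and 12".
- Data collection and management: "They will also evaluate and record the HB Grade and Lip mobility score at weeks 0, 4, 8, 10 and 12", plus baseline characteristics that are not itemised.
- Discussion: "There are differences in FEMA recovery after PFP with different disease courses", and the acknowledgement that "this study has some limitations since it is not designed for a stratified study".

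**The concern.** A subgroup analysis needs a variable measured on the trial's patients, preferably before treatment. The variable named here has no link to the eligibility rules, the outcomes or the assessments in the rest of the article. A full analysis plan that followed the sentence faithfully would inherit an analysis with no described data behind it.

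What is at stake is the standing of any subgroup result. If the sentence stays, the trial must either report that its planned subgroup analysis was not done or substitute another variable. A substitution made after outcomes have been seen would lose the value of having been planned. This matters somewhat more here because the Discussion itself says that recovery varies with disease course and that this bears on when to treat.

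**Working it through.** **Step 1. Where the named variable appears.** The sections were read for the Kellgren–Lawrence grade and for any grade the trial does use.

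| Section of the article | Kellgren–Lawrence grade | Grade or measure found |
|---|---|---|
| Inclusion and exclusion criteria | no | House-Brackmann III or above; thickness ratio at most 90% |
| Primary outcome measure | no | ultrasound thickness of two facial muscles |
| Secondary outcome measures | no | House-Brackmann I to VI; lip mobility |
| Data collection and management | no | thickness ratio, House-Brackmann, lip mobility, adverse events |
| Data processing and statistical analysis | yes, once | none |
| Abbreviations | no | House-Brackmann |

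The variable occurs once, in the sentence that plans the analysis, and has no source of data in the visible text.

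**Step 2. What the trial could use instead.** House-Brackmann grade is explicitly recorded at week 0. Checking the three-month criterion requires time since diagnosis to be ascertained at entry, but the article does not say that the date or duration is kept as a data item.

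**Step 3. The plan's own figure.** Inputs from Sample size: SD σ = 23.30, difference d = 21.54, two-sided alpha 0.05, power 0.90, dropout 10%.

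n = 2σ²(1.960 + 1.282)²/d² = 24.59, rounded up to 25 per group. Then 25/0.90 = 27.8, rounded up to 28 per group. The stated 28 is reproduced, and nothing in it depends on the subgroup sentence.

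**Step 4. What a corrected subgroup analysis could show.** Assume that σ and d apply to the outcome analysed, and that two subgroups split each group evenly. The interaction is the difference between two treatment differences, so it involves four cell means of n/2 patients each:

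SE = σ√(4/(n/2)); power = Φ(d/SE − 1.960) for an interaction of size d.

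- n = 25 evaluable per group: SE = 23.30 × √(4/12.5) = 13.18; d/SE = 1.634; power = Φ(−0.326) ≈ 37%.
- n = 28, no dropout: SE = 23.30 × √(4/14) = 12.45; d/SE = 1.730; power = Φ(−0.230) ≈ 41%.

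An interaction as large as the whole planned treatment effect is already a generous assumption. A smaller interaction or an uneven split gives less power.

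**The case against.** The strongest reply is that this is one wrong name in one sentence about a subsidiary analysis. Primary comparison, sample size, randomisation and safety are untouched, and an analysis plan or amendment could put it right. That is fair as to weight. It does not remove the error, because the article does not merely leave the subgroup variable open; it states one that does not belong to the trial as described.

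Several stronger readings are tempting, and the documents do not support them:

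- A reader might infer that none of the 56 patients will have a Kellgren–Lawrence grade. That is very likely, but the baseline characteristics are not listed and the schedule figure is not available. The supportable statement is that no visible text collects it.
- A reader might infer that the plan wrongly leaves out the relevant subgroup. The Discussion openly gives the lack of stratification as a limitation and names disease course in that context. The article does not say which variable was meant, so the defect is a wrong variable and not a proven missing analysis.
- A reader might infer that any subgroup result must now be post hoc. At the time of the article ten patients were under treatment and recruitment was to run to March 2022, so the variable could still be named before outcomes were seen.
- A reader might infer that the sentence was carried over from a protocol in another disease. That is plausible, but nothing in the article establishes it.

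**Conclusion.** The point holds in limited form. The only stated subgroup analysis rests on a grade that no visible part of the article collects or uses, and it cannot be carried out as written. This conclusion needs no outside definition of the scale. It rests on the mismatch within the article, subject to the unseen schedule figure and case report form.

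The effect on the trial's conclusions is small. The primary comparison is not affected. Even with a suitable variable, power for an interaction equal to the full planned effect is about 37% with 25 evaluable patients per group, or about 41% with all 28, assuming an even split and the planning SD. Neither the present sentence nor its replacement could settle how the effect varies with disease course. The correction is still worth making because it is cheap and because it loses its value once outcomes have been seen.

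**What to change.** Before the planned interim analysis, or any other unblinded look at outcomes, do one of two things.

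1. **Replace the variable.** Use the week-0 House-Brackmann grade, not a later value, since later values are outcomes. Add time since onset of the paralysis if the onset or diagnosis date is captured when the three-month criterion is checked; otherwise add that date to the case report form. State the categories in advance. The article supplies no cut-points, so the sponsor must choose and justify them. Two categories are preferable: an even spread over grades III to VI would leave only 28/4 = 7 patients per group in each. Test a treatment-by-subgroup interaction in whatever model is adopted for the continuous thickness ratio. The model has to be named, because the statistical section currently assigns a chi-square test to the primary outcome, and that test gives no place for such a term. Label the analysis exploratory, with no confirmatory claim.
2. **Delete the sentence** if no subgroup analysis is wanted.

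The cost is one sentence and the formal application that the section Modification of the protocol requires. Baseline House-Brackmann grade needs no new measurement; time since onset needs at most one date per patient.
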